### Intervention

Participants are randomized 1:1 to receive amitriptyline 10 mg or placebo tablets. The placebo is formulated and manufactured to match the active tablet. Study medication is dispensed and dispatched by a central dispensing pharmacy to participants’ home addresses or GP surgeries for collection.

A medication information leaflet explains how to self-­titrate over the first 2 weeks, a reminder of potential side-­effects, what to do about other medication and how to seek help. Participants are told to start taking one tablet daily, increasing by one tablet every 5–7 days up to a maximum dose of three tablets daily, as tolerated. No additional measures are undertaken to enhance adherence. Participants or their clinicians can choose to discontinue the study medication at any time. Participants are asked to stop their medication 80 days after rash onset or 70 days from starting the study medication, whichever comes sooner, to ensure a ‘­washout’ period of 10 days (the half-life of amitriptyline after a single dose is approximately 24 h)^13^ before the collection of primary outcome information at 90 days from rash onset (Figure 1).

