### Participant timeline, data collection methods and retention

Participants take part in the trial for 12 months (randomized by 31 March 2024), 6 months (randomized between 1 April 2024 and 31 January 2025) or 3 months (randomized on 1 February 2025 or later).

Most outcome data are collected by participant-­completed online or paper questionnaires, according to patient preference, with text, email or telephone reminders. All participants are asked to complete questionnaires at baseline and at 30, 60 and 90 days, and for participants with longer follow-up, at 120, 180 and 360 days. All questionnaires are dated from shingles rash onset (Figure 1).

In addition to questionnaire reminders, to encourage engagement participants are sent regular participant newsletters. In recognition of the time participants dedicate to the study, participants are sent £10 vouchers at baseline and on completion of the 90-, 180- and 360-day surveys.

Participants are contacted by a member of the research team around 7 days and 21 days after randomization. These contact points are also to support and monitor self-titration, and collect data on medication use and adverse events. If the participant or research nurse have any queries or concerns about safety, participants are offered a review with their GP surgery.

With permission, after follow-up is complete, we will extract data from the patient’s EMR for data on use of healthcare resources.

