### Statistical methods

Analysis and presentation of the trial data will be in accordance with the CONSORT^22^ and CONSORT PRO^23^ guidelines. A full analysis plan will be completed and made publicly accessible prior to analysis.

Baseline patient characteristics will be compared using descriptive statistics. Meaningful differences between the groups at baseline will inform subsequent sensitivity analyses, adjusting for imbalances.

The primary statistical analyses will be conducted on an intention-to-treat principle. The primary analysis will use logistic regression to estimate the odds ratio of PHN at 90 days after rash onset comparing the intervention and control group, adjusting for variables used in the randomization.

Repeated measures analyses will be conducted on the secondary outcomes measured at multiple follow-up ­timepoints to examine the effect of the intervention over time. These will involve logistic regression models for binary outcomes and linear regression models for continuous outcomes. Descriptive analysis of safety endpoints will be presented according to randomized group.

Because this is a pragmatic study, where participants can self-titrate the study medication as tolerated, there are no strict adherence criteria. However, participants will be included in ‘per-protocol’ analyses if they start medication within 12 days of rash onset, and report taking it every day until their scheduled stop date. Complier average causal effect analysis will investigate the efficacy of the intervention for comparison with the primary intention-to-treat effect estimate, as well as explore whether there are patient and illness characteristics associated with adherence. Sensitivity analyses will assess the robustness of the primary analysis to the impact of missing data on the primary analysis; adjustment for variables with marked imbalance at baseline; and antiviral treatment.

Subgroup analyses will examine whether the effect of the intervention on pain outcomes differs according to time from rash onset to starting treatment; daily use and total dose; and whether it is the first or second episode of shingles. Subgroup analyses will be performed by incorporating a treatment group–subgroup interaction term in the appropriate regression model. Testing will be done using the likelihood ratio test.

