Recruiting patients with incident conditions into a CTIMP in primary care is challenging. To facilitate the process, we initially relied just on EMR ‘pop-ups’ but some sites favour regular searches instead of, or alongside, this. Initially, only GPs were able to screen and refer patients but, reflecting clinical practice, this was broadened to all ‘first-contact’ healthcare professionals, including, but not limited to, advanced nurse practitioners and clinical pharmacists. We originally sought to complete participant recruitment over 18 months from 120 GP sites. However, because the number of eligible patients has been lower than expected, we extended recruitment to 37 months from over 120 group practices (>300 GP surgeries/sites). In order to complete the trial in a timely fashion, a consequence of this extension to recruitment was a reduction in the follow-up period from 360 to 180 days for patients randomized between 1 April 2024 and 31 January 2025, and 90 days for patients randomized on 1 February 2025 or later.

We aim for patients to start the study medication as soon as possible and for participants in the intervention group to take amitriptyline 30 mg daily for up to 70 days. However, because of clinical service constraints it is not always possible for participants to start taking tablets within 72 h of rash onset (as per Bowsher’s trial)^11^ and because of the uncertainty as to the minimum amitriptyline dose required to be effective, and to reduce the risk of stopping due to side-effects, participants are told to titrate their dose up to three tablets daily over the first 2 weeks as tolerated. Both of these aspects reflect current clinical care in the NHS, helping to make the findings generalizable to this setting.

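### Daily use and total dose are listed as interaction subgroups although allocation can affect both, so the planned test can show a false dose-response

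*Protocol article*

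**What the plan says.** The Statistical methods section lists the subgroup variables as "time from rash onset to starting treatment; daily use and total dose; and whether it is the first or second episode of shingles". It then fixes the model and the test: "Subgroup analyses will be performed by incorporating a treatment group–subgroup interaction term in the appropriate regression model" and "Testing will be done using the likelihood ratio test". Variables, model and test are thus all named in the article itself, not left to the analysis plan.

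How dose comes about is described elsewhere:

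- Intervention: participants start on one tablet, "increasing by one tablet every 5–7 days up to a maximum dose of three tablets daily, as tolerated". Also, "Participants or their clinicians can choose to discontinue the study medication at any time".
- Discussion: the reason given for gradual titration is "to reduce the risk of stopping due to side-effects, participants are told to titrate their dose up to three tablets daily", so side-effects are expected to bear on how much is taken and for how long.
- Participant timeline, data collection methods and retention: of the contacts around days 7 and 21 after randomization it says "These contact points are also to support and monitor self-titration, and collect data on medication use and adverse events". The schedule in Table 2 records no medication use before that.

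The Statistical methods section also plans a complier average causal effect (CACE) analysis alongside the intention-to-treat estimate. It does not say whether dose in the subgroup analysis means tablets taken in either arm or mg of amitriptyline.

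**The concern.** An interaction test compares the arms within levels of a third variable. This is a randomized comparison only if allocation does not affect that variable. Daily use and total dose do not clearly meet this condition. Only one arm receives a drug with side-effects, so the patients who stay at one tablet on amitriptyline may be of a different kind from those who stay at one tablet on placebo. If prognosis for PHN is among the differences, the contrast between arms at each dose mixes drug effect with selection.

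The Discussion says that the minimum effective dose is uncertain, so a dose-by-treatment result could be read as evidence on that question. A pattern of apparent harm at low dose and benefit at high dose could arise for a drug that does nothing to PHN. The reverse selection could hide a real gradient in a drug that works.

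**Working it through.** **Sample size.** The article gives no figure for the subgroup analyses, so its overall figure is reproduced to set the number analysed.

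- Inputs (Sample size section): 20% PHN on placebo, a 45% proportionate reduction, 90% power, 20% loss, total 846. A two-sided 5% level is assumed.
- Rate on amitriptyline: 0.20 × (1 − 0.45) = 0.11. Mean rate: 0.155.
- n per arm = [1.96 × √(2 × 0.155 × 0.845) + 1.2816 × √(0.20 × 0.80 + 0.11 × 0.89)]² / 0.09² = (1.003 + 0.651)² / 0.0081 ≈ 337.7, rounded up to 338.
- 338 / 0.80 = 422.5, rounded up to 423 per arm, or 846 in total. This matches. Evaluable: 2 × 338 = 676.

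**Simulation set-up.** There were 676 patients, 338 per arm, and 3,000 trials per scenario. Each patient has a prognostic factor u ~ N(0,1), with larger values worse.

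- Outcome: logit P(PHN) = c + g·u, with c chosen for about 20% PHN. There is no treatment term, so the drug has no effect on PHN.
- Dose (high or low): on amitriptyline, logit P(high) = 0.6 − a·u, so worse-prognosis patients are more often held at low dose. On placebo, logit P(high) = 1.4, unrelated to u.
- Analysis: logistic regression with treatment, dose group and their product; likelihood ratio test of the product at 5%; no covariates.
- Assumed, because the documents give no values: g = a = 0.5 (weak), 0.7 (moderate), 1.0 (strong).
- Same-selection rows: logit P(high) = 1.4 − a·u in both arms, with g = a = 0.7. In the last row g = a = 1.0.

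| Scenario | PHN, amitriptyline low / high | PHN, placebo low / high | Median interaction OR | Rejection |
|---|---|---|---|---|
| Dose unrelated to prognosis | 19.9% / 19.9% | 19.9% / 19.9% | 0.99 | 5.5% |
| Selection on amitriptyline only, weak | 22.3% / 18.7% | 20.0% / 19.9% | 0.80 | 8.7% |
| Selection on amitriptyline only, moderate | 24.1% / 17.4% | 19.9% / 20.0% | 0.65 | 17.1% |
| Selection on amitriptyline only, strong | 27.3% / 15.4% | 20.0% / 19.8% | 0.48 | 39.5% |
| Same selection in both arms, tablets | 25.4% / 18.4% | 25.5% / 18.3% | 1.02 | 4.9% |
| Same selection in both arms, mg (placebo = 0) | 25.5% / 18.4% | 25.5% / 18.3% | 0.66 | 26.0% |
| Prognosis-linked variable, same link in both arms (as for time to first tablet) | 29.7% / 16.7% | 29.7% / 16.8% | 0.99 | 5.6% |

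The simulation standard error at 5% is √(0.05 × 0.95 / 3000) = 0.4 percentage points, so 4.9% to 5.6% is consistent with nominal size.

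**Reading the moderate row.** The apparent odds ratio at low dose is (0.241/0.759) / (0.199/0.801) = 1.28. At high dose it is (0.174/0.826) / (0.200/0.800) = 0.84. The true value is 1 at both.

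**Why mg coding fails even with equal selection.** With placebo set to zero, the dose term contrasts high-dose with low-dose amitriptyline patients directly: (0.184/0.816) / (0.255/0.745) = 0.66. The same gradient exists on placebo, but the model has no term that removes it.

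**The case against.** The strongest reply is that being measured after randomization does not by itself bias an interaction test, and this is correct. The test kept its size when dose was unrelated to prognosis, even though fewer amitriptyline than placebo patients reached high dose. It also kept its size when selection was equal in both arms and dose was counted in tablets. Bias needs dose to be linked to prognosis, and either a link that differs by arm or mg coding. The documents make a differing link plausible but do not establish its strength.

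Three stronger readings are tempting and are not supported.

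- **Time to starting treatment.** A reader might infer that it is invalid for the same reason. However, it is settled before any drug exposure, the tablets match (Intervention), and participants, treating clinicians and the research team are masked (Masking). Allocation should not affect it among starters, and a variable of this kind gave 5.6% rejection. What remains is that never-starters have no value.
- **Pain-driven dosing on placebo.** A reader might infer that placebo patients titrate to their pain. That assumption gives 14% to 57% rejection in an unadjusted model, but the article describes one tolerability-based schedule for both arms and nowhere says that dose follows pain.
- **Damage to the main result.** The primary analysis is by intention to treat and does not use dose.

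The reply that the figures ignore covariates also has force. The primary model adjusts for the randomization variables, which include entry pain (Allocation), and the subgroup models may do so too. This was checked only under the pain-driven assumption, with 1,500 trials per scenario. Rejection of 14.5%, 37% and 61% fell to 6.5–10%, 15–26% and 20–38%, depending on how closely entry pain tracks prognosis (assumed correlation 1.0 to 0.7). A fall in the same direction is expected under the side-effect mechanism, but its size was not computed.

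**Conclusion.** The point holds for daily use and total dose only. As specified, their interaction tests need not compare like with like. They can reject well above 5% for a drug that has side-effects but no effect on PHN: about 9% to 40% in the scenarios shown. That range is an illustration. It rests on worse-prognosis patients tolerating amitriptyline less well, on assumed strengths of that link, and on an unadjusted model. It would be lower with adjustment for entry pain, and the excess disappears when selection is equal across arms and dose is counted in tablets. The simulations show the false-gradient direction; the masking of a real gradient follows from the same mechanism but was not simulated.

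This should be fixed, but it does not threaten the trial's main conclusion: the primary intention-to-treat analysis and the sample size of 846 stand.

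**What to change.** Before unmasking, in the Statistical methods text and the analysis plan:

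1. Remove daily use and total dose from the interaction subgroups. Keep first or second episode.
2. Address exposure through the planned CACE (instrumental-variable) analysis, with amitriptyline tablets or days taken as a graded exposure and allocation as the instrument. Zero exposure on placebo is legitimate there, because allocation and not dose carries the comparison.
3. State that this gives an average effect per unit of exposure. It assumes that allocation acts on PHN only through the amount taken and that the effect is linear in that amount. It is not a dose-response curve.
4. Label any table of outcome by dose as descriptive and non-randomized.
5. Optionally, use or add time from rash onset to randomization, which is defined for never-starters too. It leaves out the delay between randomization and the first tablet, so adding it may be preferable to replacing time to starting treatment.

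The cost is wording only, with no new data and no change in sample size. The trial gives up a formal test of effect by dose, which the stated method could not validly provide.

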### Monitoring

For the duration of the study, the independent Data Monitoring Committee (DMC) and Trial Steering Committee will meet regularly and monitor the study, to ensure it is conducted according to good research practice.

We will regularly monitor the characteristics of screened, referred and randomized patients; and data completeness, participant retention and the proportion of participants reporting PHN and adverse events. In closed meetings with the DMC, the unmasked junior statistician will provide these data by allocation.

An annual Development Safety Update Report is submitted to the Medicines and Healthcare products Regulatory Authority (MHRA) until the end of the trial is declared.

### Harms

It is anticipated that most adverse events will be detected via the questionnaires administered at the follow-up timepoints.

Pharmacovigilance will be carried out in accordance with the guidance set out by the European Commission Detailed Guidance CT-3 2011, and the requirements of the Medicines for Human Use (Clinical Trials) Regulations.

### Auditing

Auditing will be independently undertaken by University Hospitals Bristol and Weston (UHBW) National Health Service (NHS) Foundation Trust on behalf of the sponsor. A Trial Monitoring Plan has been developed by UBHW and agreed by the sponsor, Trial Management Group and chief investigator based on the trial risk assessment.

### Trial registration

The trial registration numbers are EudraCT 2021-001101-78 and ISRCTN14490832.

## Health economics

The primary analyses will present cost-effectiveness (in terms of cost per case of PHN prevented) and cost–­utility analysis from an NHS and personal social services perspective at 90 days. For the cost–utility analysis, QALYs will be estimated using utility scores derived from the 5-level EQ-5D (EQ-5D-5L) and valued by application of the National Institute for Health and Care Excellence (NICE)-recommended value set approach at the time of analysis.^24^ Secondary analysis will consider if the effect is sustained over 12 months.

Resource-use data will be collected from EMR and participant questionnaires, using a ModRUM core healthcare module and bespoke questions covering social care, informal care, personal expenses and usual activities.^20^ The questionnaire and EMR (where feasible to categorize) data will focus on resource use relevant to shingles pain. Further detail will be prespecified in the Health Economics Analysis Plan. Resources will be valued using nationally available sources of unit costs.

Where relevant, incremental cost-effectiveness ratios will be estimated for cases of PHN prevented and QALYs gained. The incremental net monetary benefit will be estimated at willingness-to-pay thresholds of £20 000 and £30 000 per QALY. Statistical methods will deal with skew, baseline imbalance, missingness and sampling uncertainty as appropriate. Cost-effectiveness acceptability curves will show the probability that amitriptyline is the optimal choice over a range of possible values of the ceiling ratio.

## Qualitative study

### Phase 1: support and optimize delivery of the trial

Initially, qualitative work will focus on identifying potentially modifiable barriers to recruitment, along with exploring initial acceptability of the intervention.

The first is done by reviewing a sample of audio-recordings of recruitment conversations undertaken by researchers and other staff as part of the two-step deferred consent process. Summaries of factors identified that may help or hinder recruitment, and how the latter could be modified, are fed back to recruiting staff.

Next, brief (5–20 min) telephone interviews are conducted with up to 20 staff who have been involved in identifying and recruiting patients, and up to 20 patients (within 1 month of them presenting to their GP) who have consented to participate, declined or withdrawn from the trial during the internal pilot phase. These interviews are exploring understanding of the trial; factors that influence recruitment; and views of intervention acceptability.

### Phase 2: acceptability and perceived effectiveness of the intervention

In the main trial phase, qualitative work focuses on understanding acceptability and perceived effectiveness of the intervention, to aid interpretation and implementation of the trial findings.

We are conducting semi-structured telephone interviews with up to 30 patients (to achieve sufficient information power)^25^ at around 2 months postrandomization. Patients are purposefully sampled across intervention and control groups to ensure variation in age, sex, pain severity and adherence. We aim to include patients who stop treatment or drop out of the trial with an exploration of reasons why they drop out.

In interviews, we are exploring patients’ understanding and experiences of the intervention, focusing on perceptions of amitriptyline, experiences of self-titration and alterations in dosage, experiences of side-effects, and impact on willingness to continue treatment and stay in the trial.

Interviews in both phases are audio-recorded and transcribed verbatim. Analysis will be thematic, using a combination of inductive and deductive coding.

## Ethics and dissemination

### Protocol amendments

The sponsor can make a nonsubstantial amendment at any time during a trial. For substantial amendments to the Clinical Trial Authorisation (or the documents that supported the original application) or to the research ethics committee (REC) application (or supporting documents), the sponsor will submit a valid notice of amendment to the MHRA or REC respectively.

### Consent

On receipt of a referral, the potential participant is sent the full Participant Information Leaflet. A researcher arranges a time to speak with them (by telephone, video call or, where necessary, in person), to ensure full understanding of the study and any questions will be answered. Consent will mostly be online,^26^ but for people unable to do this, written consent will be received in person or by post.

### Confidentiality

Information from participants will only be identifiable via a unique study identification number. Participant data will be securely stored in locked cabinets and on University of Bristol servers.

Personal data will not be kept for longer than is required for the purpose for which it has been acquired. Research data will be kept for at least 15 years, when all paper records will be destroyed by confidential means.

Interview data captured on the encrypted audio-recorder will be transferred to a University of Bristol computer as soon as possible after each interview. Audio recordings will be transcribed by university-approved transcription services. Transcripts will be labelled with a study-assigned participant number, edited to ensure the anonymity of respondents and stored securely.

### Ancillary and post-trial care

Prescriptions for amitriptyline after the intervention phase are the responsibility of the participant’s normal clinician, but can only occur after collection of the primary outcome at 90 days after shingles rash onset.

### Dissemination policy

A plan for disseminating the trial results will be developed by the Trial Management Group. Initial findings will be submitted to relevant national and international meetings. Participants will be sent a lay summary and the results of the study will be published in peer-reviewed journals.

